### Assessments, measurements, diagnostic procedures and data collection

Recruitment started on 17^th^ January 2023. Upon recruitment, after the participants themselves and their parents/caregivers have agreed to participate in the study and signed the informed consent form, participants will undergo a physical examination, anthropometric measurements (height and weight for calculation of BMI and BMI percentiles, hip and waist circumference measurement, body composition assessments by Tanita MC-780MA multi frequency segmental body composition monitor based on bioelectrical impedance analysis (BIA) and by 7-site skinfold measurement using Harpenden skinfold caliper) along with other routine diagnostic tests as part of their asthma management plan, such as allergy tests (skin prick test and total and allergen-specific immunoglobulin E in the serum), lung function and bronchial challenge tests (spiroergometry) etc. Additionally, whole blood samples will be taken for subsequent transcriptomic analysis and isolation of PBMCs (peripheral blood mononuclear cells), as well as stool samples for metagenomic analysis of the gut microbiome. Blood samples leftover after routine diagnostic tests (blood count, lipid profile, glucose level etc. (Table 1) will be stored at -20°C for subsequent genetic analysis or at -80°C for evaluation of systemic inflammation. Stool samples will be stored at -20°C for subsequent microbiome analysis. Other relevant clinical data and data such as personal and family history, and demographics will also be collected.

**Table 1 pone.0306400.t001:** Features used in this study.

Baseline demographics	Gender, age
**Subjective clinical data**	Personal and family medical history, atopy status, allergic rhinitis (AR), atopic dermatitis (AD), food allergy and other comorbidities
**Objective clinical data**	Skin prick and total and specific e.g. test results, hematologic and biochemical blood test results (blood count, lipidogram, glucose level, creatinine, urates, total bilirubin, ALT^1^, AST^1^, GGT^1^, ALP^1^, electrolytes), urine analytes (with ketone bodies), comorbidity (ENT^2^ examination, pH probing with impedance for the reflux episodes monitoring for diagnostics of GERD/LPR^3^, other) lung function testing, FENO^4^, bronchial challenge tests, spiroergometry, treatment used, nutritional status (vitamins, minerals)
**Anthropometric data**	Height, weight, BMI^5^, BMI percentile for children, hip and waist circumference and hip/waist ratio, body composition (% fat mass, % fat free mass)
**Systemic inflammation data**	hsCRP^6^, leptin, other serum markers
**Genetic data**	Epigenetic status (DNA^7^ methylation), genetic expression patterns, gut microbiome
**Dietary data**	Dietary intake, food diaries, dietary questionnaires

^1^Liver enzymes (Alanine Aminotransferase, Aspartate transaminase, Gamma-glutamyl transferase, Alkaline phosphatase).

^2^Ear, Nose, and Throat examination.

^3^Gastroesophageal reflux disease/laryngopharyngeal reflux.

^4^Fraction of Exhaled Nitric Oxide.

^5^Body Mass Index.

^6^C-reactive protein.

^7^deoxyribonucleic acid.

Their dietary patterns and food intake will be assessed by food frequency questionnaire (FFQ), 14-point Mediterranean Diet Adherence Screener- MEDAS (or children version – KIDMED), The Three-Factor Eating Questionnaire (TFEQ-R1) and 3-day food diary at the beginning and end of the study.

Participants will be assigned specific and adapted physical exercise programmes and vital and other parameters (heart rate, respiration, step count etc.) will be collected by smart bands.

### Follow up

Participants will be followed up at regular intervals. Every two months they will undergo a medical physical examination and anthropometric measurements once a month (as discussed in the previous section) and any adverse events recorded on adverse events reporting forms will be discussed. Additionally, their dietary intake and study compliance will be assessed by 3-day food diary and 24-hour dietary recall in each phase of the study. For better adherence to the programme, individual nutritional consultations will be carried out if needed.

After 1, 3, 6, 9 months and at the end of the study, the participants will have blood and urine samples collected. At these timepoints, the participants health status, nutritional status and level of systemic inflammations will be assessed. Stool samples will be taken at baseline and at the end of the study. Design and key timepoints of the study are presented in Fig 1.

**Fig 1 pone.0306400.g001:**
[figure not shown]
Study design and key timepoints.

The appearance of any exclusion criteria during the follow up phase will be a signal for participant exclusion from the study. During the entire course of the study, it will not be allowed to use other weight loss methods such as weight-loss medications or bariatric surgery.

Upon recruitment, participants will be randomized into 3 groups, according to weight loss plan: innovative formulation (1); standard (2) and control group (3) in a ratio of 2:2:1, respectively. Stratified randomization according to age, sex and baseline BMI will be provided to secure balanced groups according to their characteristics at baseline. Randomization plan will be done by the independent statistician not involved in recruitment and participants assessment prior to any recruitment. Trial participants, principal researchers, outcome assessors and data analysts will be blinded after intervention group allocation. Unblinding is permissible in case of severe adverse events or study withdrawals.

**Innovative group (1):** participants will use the innovative line of products intended for body weight reduction, that represent a meal replacement for weight management (liquid formulations and powders for resuspension- shakes and soups)- test group;**Standard group (2):** participants will use the standard line of products intended for weight reduction that represent a meal replacement for weight management with already proven clinical effectiveness (positive control);**Control group (3):** participants will receive personalized programme for a reduced low-calorie diet (balanced nutrition).

The standard product line will contain common ingredients and is currently commercially available [10], while the innovative product line differs will implement raw materials that are considered better sources of potentially bioactive components. Clinical studies suggest that these ingredients could have more health benefits due to their anti-inflammatory and antioxidant properties, including an impact on clinical parameters of the metabolic syndrome that is increasingly present in obese individuals [11].

All participants will implement physical activity regimes, personalized according to age, gender, health status, BMI, body composition, current physical fitness etc.

The study protocol is defined in detail in Supplementary material. This study will encompass 4 phases of different duration and design for adults and pediatric participants): initial phase (intensive), active phase, stable phase and monitoring phase, preceded by an entry phase of adaptation to the study protocol (duration of entry phase: 2 weeks). The study phase diagram is shown in Fig 2.

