### Study endpoints

The primary endpoint of this study is to determine the effectiveness of a weight reduction diet program based on an innovative and standard product line (meal replacements) through actual reduction of the body mass (BM)/ fat mass (FM) of the participants in relation to their pre-trial body mass (BM)/fat mass (FM).

The secondary study endpoints include:

reduction of waistline and reduction of waist/hip and waist/height ratio;improvement of the participants` lipid profile (increase in HDL/LDL ratio) compared to initial values;improvement of the quality of life of participants;improvement of asthma control, decrease in the number and severity of asthma exacerbations in participants with asthma;decrease in systemic inflammation, decrease in oxidant stress biomarkers.

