**Fig 2 pone.0306400.g002:**
[figure not shown]
Study phase diagram for active group (innovative and standard). Control group (not shown) has 5 regular low-calory balanced meals throughout the entire course of the study. In each phase. exercise and sufficient fluid intake are required.

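### The protocol calls trial participants blinded without exception, but participants can be blinded only between the two meal-replacement arms, not in either comparison with the diet-only control

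*Protocol article*

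**What the plan says.** The Follow up section of the protocol article (text after Fig 1) randomises participants to "innovative formulation (1); standard (2) and control group (3) in a ratio of 2:2:1, respectively". It then says: "Trial participants, principal researchers, outcome assessors and data analysts will be blinded after intervention group allocation". The sentence names four roles and applies to the whole trial. The next sentence adds: "Unblinding is permissible in case of severe adverse events or study withdrawals".

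The same section describes the three arms:

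- **Innovative:** a product line "that represent a meal replacement for weight management (liquid formulations and powders for resuspension- shakes and soups)- test group".
- **Standard:** "participants will use the standard line of products intended for weight reduction that represent a meal replacement for weight management".
- **Control:** "participants will receive personalized programme for a reduced low-calorie diet (balanced nutrition".

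The Fig 2 legend treats the innovative and standard arms together as the active group and sets control apart: "Control group (not shown) has 5 regular low-calory balanced meals throughout the entire course of the study".

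The primary endpoint in Study endpoints is change in body mass and fat mass. The secondary endpoints include "improvement of the quality of life of participants" and asthma control with the number and severity of exacerbations.

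**The concern.** A participant who eats ordinary meals all through the study knows that they are in neither product arm. A participant who receives shakes and soups knows that they are not in control. For one of the four named roles, the blinding statement therefore claims something that the design cannot deliver in any comparison with control.

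What is at stake is how the control comparisons are read. Participants report their own quality of life and some aspects of asthma control, and those reports can shift when people know they were given the programme's products or only a diet plan. Knowing the arm can also affect effort with diet and exercise, and willingness to stay in the study. A reader who relies on the blinding sentence would rate these comparisons as better protected from bias than they are.

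**Working it through.** No figure in the plan has to be reproduced. The check sets the arm descriptions against the blinding sentence.

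**Step 1: what each arm visibly receives.**

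| Arm | Meal-replacement product | Source |
|---|---|---|
| Innovative | Yes | Follow up, arm description |
| Standard | Yes | Follow up, arm description |
| Control | None named; five ordinary meals, no sham described | Follow up, arm description; Fig 2 legend |

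That control receives no product is an inference. The text does not say it in those words, but both descriptions of the arm point to it and nothing contradicts it.

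**Step 2: can participants be blinded, comparison by comparison?**

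| Comparison | Can participants be blinded? | Reason |
|---|---|---|
| Innovative vs standard | Possible | Both arms use meal replacements |
| Innovative vs control | No | Product against ordinary meals |
| Standard vs control | No | Product against ordinary meals |

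So 2 of the 3 pairwise comparisons cannot be blinded to participants.

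**Step 3: which of the four named roles does the text contradict?**

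- *Trial participants:* contradicted, for both comparisons with control.
- *Principal researchers:* not shown to be contradicted. Nothing says that they hand out products or deliver diets.
- *Outcome assessors:* not contradicted. Someone who weighs a participant or runs bioimpedance need not know the diet.
- *Data analysts:* not contradicted. The 2:2:1 ratio (88:88:44 in Statistical analysis) would make control recognisable by size in coded data, so masking here needs some care, but the text does not rule it out.

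Staff who give nutritional consultations or review food diaries will see who uses products. They are not on the blinded list, so their knowledge contradicts nothing. It is still a route by which expectation can reach the participant.

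**Step 4: which outcomes are exposed in the control comparisons?**

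- *Most exposed:* quality of life and the participant-reported part of asthma control.
- *Less exposed:* body mass and fat mass. The Assessments section measures these by weight, bioimpedance and skinfold caliper, so a masked assessor protects the measurement. Behaviour that depends on knowing the arm can still affect the true value.

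**The case against.** The strongest reply is that only one of the four roles is contradicted. Assessors and analysts can be masked in every comparison, the primary endpoint is measured rather than reported, and the article never describes the trial as fully blinded. It also refers to supplementary material, not shown here, for detail. Most of this stands, and it limits the point to participants and the staff who deliver the interventions. It does not remove the contradiction. The article makes a positive statement about participants that its own arm descriptions rule out, and further detail elsewhere could not make that statement true for the control comparisons.

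A reader might draw three stronger conclusions that the document does not support.

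- **That comparisons with control are open-label throughout.** This goes too far, because assessor and analyst masking remains possible.
- **That unblinding at withdrawal serves no safety purpose and should be removed.** The Follow up section makes the appearance of any exclusion criterion a signal for exclusion. The adult criteria include pregnancy, systemic corticosteroid use and a recent asthma-related emergency visit. Some withdrawals can therefore be health-related without being severe adverse events. Unblinding is also permitted, not required.
- **That the 15% drop-out rate gives 33 (0.15 × 220) to 36 (0.15 × 240) participants unblinded without a safety reason.** Controls have no product blind to break. For the product arms alone (four fifths of the sample: 176 of 220, or 192 of 240) the figures are 0.15 × 176 = 26.4 and 0.15 × 192 = 28.8. Even these are ceilings, since they assume that every drop-out is unblinded and that none has a health reason. The document states neither.

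**Conclusion.** The point holds in a limited form. The statement that trial participants are blinded is true at most for innovative versus standard. It cannot be true for either comparison with control, which is two of the three pairwise comparisons. Quality of life and the participant-reported part of asthma control are open to expectation effects there.

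The size of the control arm (44 of 220, one fifth) does not measure the problem, because product-arm participants know equally well that they are not controls. The document gives no basis for estimating how large any bias would be, so none is claimed.

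The conclusion rests on two assumptions: control receives no meal-replacement or sham product, and at least part of asthma control is reported by participants. The article does not name the instrument.

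**What to change.** Replace the single blinding sentence with one that goes by role and by comparison:

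- **Innovative vs standard:** participants, principal researchers, outcome assessors and data analysts blinded.
- **Each comparison with control:** not blinded to participants or to staff who deliver the diet or products; outcome assessors and data analysts kept masked. Say whether principal researchers take part in delivery, and so whether they are masked here.

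Then state that participant-reported outcomes compared with control will be reported and interpreted as unblinded.

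Keep the asthma endpoints as they stand. Lung function or FENO should not replace asthma control in these comparisons: the Follow up section lists no repeat of either, and the substitution would displace a stated secondary endpoint.

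The cost is a weaker but accurate blinding claim. The change is to wording and reporting, with some attention to keeping assessors apart from dietary contact. Arms, products, visits and sample size are unaffected.

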**Fig 2 pone.0306400.g002:**
[figure not shown]
Study phase diagram for active group (innovative and standard). Control group (not shown) has 5 regular low-calory balanced meals throughout the entire course of the study. In each phase. exercise and sufficient fluid intake are required.

### Statistical analysis

Sample size was calculated as 88: 88: 44 (N = 220 with the test for repeated measures using effect size of D = 0.5 (which represents a medium size clinical effect), SD = 1, power = 0.8 and alpha = 0.05 (minimum group size of 34) using a 15% drop-out rate. Analysis of variance for repeated measurements will be used to determine the effectiveness of individual programs on primary outcomes (BM/FM). The same analysis will be used to analyze secondary performance parameters and safety parameter variables. A chi-square test or Fisher’s test will be used to compare the occurrence of safety-related parameters between groups. The threshold for missing values will be set at 5%. If the missing values for certain variables exceed this threshold, these will be handled by imputing variables according to previously measured or observed values, that is the last observation will be carried forward. The analysis will be done as intention-to-treat (ITT) and as per-protocol (PP). P < 0.05 will be considered statistically significant with appropriate correction for multiple comparisons. The statistical analysis will be performed using STATISTICA 12 program (StatSoft, Tulsa, OK, USA).

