### Study population

Overweight and obese participants (adults and children) will be recruited in a prospective interventional case-control clinical study at the Outpatient clinical at Srebrnjak Children`s Hospital, Zagreb, Croatia. The sample size is set to 240 participants, adults (>18 years) and children aged 12-18 years, with 1/3 of the participants being children (approximately 160 adults and 80 children). Written informed consent will be obtained from all participants and their parents/caregivers. The study was approved by the local Ethics committee at SCH (on 14^th^ March 2022, Ref. no.: 04-301/1-22; Supplementary material). The study has been registered at ClinicalTrials.gov PRS (ID: NCT05980663, NCT05733871).

The study involves participants (adults and children aged 12 to 18 years, of both sexes) who have themselves signed a written informed consent (for pediatric participants both the children and their parents/caregivers will sign the informed consent, according to local legislation), i.e., those who agreed to participate in the study and do meet the criteria for inclusion. The participants will be assessed for inclusion and exclusion criteria on their first study visit after signing the informed consent. Criteria for inclusion and exclusion will be assessed by a specialist physician (pediatric allergy specialist) and an occupational medicine specialist.

The main inclusion criteria are overweightness and obesity (for adults- BMI > 27 kg/m^2^, for children- ≥ 90^th^ BMI percentile), to be able to correct for differences in body composition (e.g., higher BMI due to higher muscle mass in semi-professional or professional athletes). Additional inclusion criteria will include: physician diagnosed asthma (according to ERS/ATS guidelines) for at least one year, being on a stable dose of anti-inflammatory treatment for at least one month according to GINA (Global Initiative for Asthma) guidelines [8,9], clinically significant allergy to indoor and outdoor allergens, with positive skin prick test (SPT) and specific IgE levels (>0.7 kUA/L).

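### The sample-size figures 34, 220 and 240 do not fit together, and the stated 80% power is not shown for the randomised comparison with control

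*Protocol article*

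**What the plan says.** All of this is in the protocol article.

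- **Statistical analysis** gives the calculation: "Sample size was calculated as 88: 88: 44 (N = 220 with the test for repeated measures", then the inputs "power = 0.8 and alpha = 0.05 (minimum group size of 34) using a 15% drop-out rate". The effect size is tied to a repeated-measures test: "with the test for repeated measures using effect size of D = 0.5", with an SD of 1.
- The same section plans repeated-measures ANOVA for the primary outcomes, both ITT and per-protocol analyses, and last observation carried forward when missing values exceed 5%. On significance it says: "P < 0.05 will be considered statistically significant with appropriate correction for multiple comparisons".
- **Study population**: "The sample size is set to 240 participants". It does not mention 220.
- **Follow up** randomises participants 2:2:1 to innovative product, standard product and diet control.
- **Study endpoints** words the primary endpoint as a reduction in body mass or fat mass relative to each participant's own pre-trial value.
- **Discussion** says that recruitment will be enlarged to allow for drop-outs, although the 220 is already described as using the 15% rate.

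The article does not state whether the test is one- or two-sided, what the SD of 1 refers to, the within-person correlation, or which comparison the 80% applies to.

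**The concern.** The trial is randomised with a control arm half the size of each active arm, so the comparison with control has the least power. The sample-size statement gives one power figure and does not say what it is for. A reader will naturally take it as the power of the randomised comparison. The group size behind it matches a before-after test within one arm, which makes no use of the randomisation. The steps from that group size to the total, and from the total to planned enrolment, do not follow either.

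If the figures stay as they are, a null result against control could be read as coming from a trial shown to have 80% power for that comparison. The document does not show this.

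**Working it through.** **Inputs.** From Statistical analysis: D = 0.5, SD = 1, power 0.80, alpha 0.05, minimum group 34, drop-out 15%, 88:88:44 = 220. From Study population: 240, which at 2:2:1 is 96:96:48. Assumed here: two-sided testing, and SD = 1 as the SD of the analysed change. Power is from the noncentral t distribution.

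**Step 1: reproduce 34.** One group, before-after: noncentrality = d√n, df = n − 1.
- n = 33: power 79.5%
- n = 34: power 80.8%

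So 34 is the before-after size for the stated inputs.

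**Step 2: size for two arms.** Noncentrality = d√(n₁n₂/(n₁ + n₂)), df = n₁ + n₂ − 2.
- 64:64 gives 80.2%
- 96:48 gives 80.2%
- 34:34 gives 53%
- 68:34 gives 65%

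34 is not a between-arm size.

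**Step 3: from 34 to 220.**
- 34/0.85 = 40.0 (34 × 1.15 = 39.1, also 40 when rounded up)
- At 2:2:1 this is 80:80:40 = 200, not 88:88:44 = 220
- Going from 34 to 44 implies a loss of 1 − 34/44 = 22.7%, not 15%

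**Step 4: from 220 to 240.**
- If 220 were the evaluable number, 15% loss would need 220/0.85 = 258.8, so 259
- 240 implies a further allowance of 1 − 220/240 = 8.3%

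Neither matches the stated 15%.

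**Step 5: power of either active arm against control at d = 0.5.** After 15% loss, 88 × 0.85 = 74.8 and 44 × 0.85 = 37.4 (taken as 75:37); 96 × 0.85 = 81.6 and 48 × 0.85 = 40.8 (taken as 82:41).

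| Enrolled | Analysed (active:control) | alpha 0.05 | alpha 0.05/3 |
|---|---|---|---|
| 220 | 88:44, everyone | 76.7% | 61.2% |
| 220 | 75:37, after loss | 69.4% | 52.5% |
| 240 | 96:48, everyone | 80.2% | 65.8% |
| 240 | 82:41, after loss | 73.7% | 57.5% |

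The last column is an illustration (Bonferroni over three pairs); the plan names no method.

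**Step 6: the other comparisons, after loss.**
- Before-after in the control arm, the smallest: 84% (n = 37) and 88% (n = 41)
- Innovative against standard: 86% (75:75) and 89% (82:82)

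**Step 7: sensitivity to the assumptions, after loss, N = 220 / N = 240.**
- One-sided 0.05 against control: about 80% / 83%
- If D is in units of the raw SD, the SD of change is √(2(1 − ρ)), where ρ is the within-person correlation. Change-score power against control is 55% / 59% at ρ = 0.3, 70% / 73% at 0.5 and 89% / 92% at 0.7 (unrounded arm sizes). The SD of change equals 1 at ρ = 0.5
- Baseline-adjusted analysis at ρ = 0.5: 82% / 85%

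**The case against.** The tempting stronger reading is that the trial fails to deliver its 80% power. The document does not support that.

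- **The 80% is not tied to the control comparison.** The primary endpoint is worded as change from the participant's own baseline, and for that contrast 34 is correct and every arm exceeds 80% after loss. This stands. What remains is that the plan does not say which comparison the figure covers, and that a before-after test does not evaluate one randomised arm against another.
- **69% and 74% are completers' figures.** The plan includes an ITT analysis with last observation carried forward. If all 240 are analysed, power against control is 80%. This stands, so both sets of figures belong in the statement. The plan also has a per-protocol analysis and itself expects 15% loss.
- **One-sided testing could explain 220.** With the normal approximation, a one-sided 0.05 test at 2:1 needs 37.1 controls, and 37.1/0.85 = 43.6, which rounds up to 44 and gives 88:88:44. That is possible, but no one-sided test is stated, and it contradicts the printed "minimum group size of 34".
- **34 has another possible source.** An omnibus repeated-measures ANOVA with three equal groups, f = 0.25, four visits and correlation 0.5 also gives 34 per group. Those inputs are not in the document, and this calculation does not establish 80% for a comparison with the smaller control arm.
- **240 exceeds 220.** A reader might infer a recruitment shortfall. There is none; it is an unexplained difference.
- **The multiplicity method may be set out elsewhere.** True, and the choice of Bonferroni is only an example. But the calculation uses alpha 0.05 while the same section promises a correction, and any correction lowers power.

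A fuller protocol is said to be in the supplementary material. It may explain the calculation, but the printed figures still contradict one another.

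**Conclusion.** The point holds as an inconsistency in the sample-size statement and an 80% that is not shown for the randomised comparison with control. It is not a demonstrated failure of power.

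The inconsistency needs no assumption about the SD or the correlation: 34 with 15% drop-out leads to 200, not 220, and 240 is not linked to either. That 34 is a before-after size and not a between-arm size follows from the stated inputs with two-sided testing.

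The power against control is conditional. With two-sided alpha 0.05 and SD = 1 as the SD of the analysed change, it is 77% (N = 220) or 80% (N = 240) with everyone analysed, and about 69% or 74% after 15% loss. Under other readings of the SD or the sidedness it falls on either side of 80%, which is why those inputs have to be stated. Correction for multiple comparisons would lower each figure.

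**What to change.** Keep enrolment as planned and rewrite the statement:

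1. Give one N in both Study population and Statistical analysis: 240 = 96:96:48.
2. Label 34 as the before-after size within one arm, or delete it, and correct the drop-out arithmetic.
3. Name the comparison, the sidedness and the alpha that the 80% covers, and say what the SD of 1 refers to.
4. Report power for an active arm against control at N = 240: about 80% if all are analysed and about 74% after 15% loss, with the assumptions stated. Add the figure at the corrected alpha that will be used.

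The cost is wording only, with no extra participants. The one downside is a less favourable stated power.

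### The minimum group size of 34 for 80% power is what a one-arm before-after test needs with the printed inputs, so the 80% is not shown to hold for the randomised comparisons with control

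*Protocol article*

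**What the plan says.** The Statistical analysis section of the protocol article gives the whole calculation in one sentence. It opens "Sample size was calculated as 88: 88: 44 (N = 220", names the method and effect as "with the test for repeated measures using effect size of D = 0.5 (which represents a medium size clinical effect), SD = 1", sets "power = 0.8 and alpha = 0.05", and reports a "minimum group size of 34" with 15% drop-out. It does not say whether D is a change within one arm or a difference between arms. It does not say whether the SD is that of the raw measurement or of the change. It gives no number of measurements, no correlation and no sidedness.

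The design is in the Follow up section: participants are randomised to "innovative formulation (1); standard (2) and control group (3) in a ratio of 2:2:1, respectively". The innovative line is the test arm, the standard line is a positive control, and the control arm follows a personalised low-calorie diet. All arms take part in physical activity programmes.

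Three other statements bear on the calculation:
- Study endpoints defines the primary endpoint as reduction in body mass or fat mass against the participant's own pre-trial value.
- Study population sets the sample at 240, not 220.
- Statistical analysis promises a correction for multiple comparisons but does not name the method.

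**The concern.** A reader of a randomised three-arm trial will take a stated 80% as the chance of showing that a product arm beats control. With the inputs as printed, 34 is instead the number needed to detect a before-after change in a single arm.

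The two quantities differ in substance as well as in size. Controls also eat a low-calorie diet and exercise, so they can be expected to lose weight. A within-arm change of 0.5 SD would not carry over in full to a difference between arms. Only the randomised contrasts can separate the effect of the products from that of the common programme. If the 80% does not belong to them, a null result against control would be credited with more power than the plan has shown.

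**Working it through.** **Inputs.** D = 0.5, SD = 1, power 0.8, alpha 0.05, arms 88:88:44, drop-out 15% (Statistical analysis); allocation 2:2:1 (Follow up); 240 participants (Study population). Two-sided testing is assumed.

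**Step 1: reproduce 34.** For a paired or one-sample t-test the noncentrality is D√n / SD on n − 1 degrees of freedom.
- n = 33: 0.5 × √33 = 2.87, power 0.795
- n = 34: 0.5 × √34 = 2.92, power 0.808

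The exact solution is n = 33.4, so the minimum is 34. No input beyond those printed is needed.

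**Step 2: the same inputs for two arms.** The noncentrality is D / (SD × √(1/n₁ + 1/n₂)) on n₁ + n₂ − 2 degrees of freedom. For 80% power this needs 64 + 64 at equal allocation, or 96 + 48 at the 2:1 product-to-control ratio.

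**Step 3: completers.** From 220: 88 × 0.85 = 74.8 and 44 × 0.85 = 37.4, so about 75:75:37. From 240 at 2:2:1 the arms are 96:96:48; 96 × 0.85 = 81.6 and 48 × 0.85 = 40.8, so about 82:82:41.

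**Step 4: power of the randomised contrasts, if 0.5 is the between-arm difference and SD = 1 is the SD of the analysed change.** Both readings are assumptions. The correction is unnamed, so Bonferroni is also an assumption.

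| Contrast | Completers | Alpha 0.05 | Alpha 0.05/2 | Alpha 0.05/3 |
|---|---|---|---|---|
| Product vs control | 75:37 | 69% | 59% | 53% |
| Product vs control | 82:41 | 74% | 64% | 57% |
| Innovative vs standard | 75:75 | 86% | 79% | 74% |
| Innovative vs standard | 82:82 | 89% | – | 78% |

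With no loss at all, product vs control has 77% at 88:44 and 80% at 96:48, unadjusted.

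The difference from control detectable with 80% power is about (t critical value + 0.84) × √(1/n₁ + 1/n₂). At 75:37 that is (1.98 + 0.84) × 0.201 = 0.57 SD. At 82:41 it is (1.98 + 0.84) × 0.191 = 0.54 SD.

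**Step 5: power at 75:37 if SD = 1 is the raw SD.** With baseline correlation ρ, the SD of the change is √(2(1 − ρ)) and the ANCOVA residual SD is √(1 − ρ²). Unadjusted, two-sided 0.05:

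| ρ (assumed) | Change score | ANCOVA |
|---|---|---|
| 0.3 | 55% | 73% |
| 0.5 | 69% | 81% |
| 0.6 | 79% | 87% |
| 0.7 | 89% | 93% |

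Power can therefore fall on either side of 80%, and the article gives nothing that fixes where.

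**The case against.** **34 does not uniquely identify a paired test.** This stands. With SD = 1 as the raw SD, a between-arm change-score comparison also needs 34 per equal arm at a correlation of about 0.74, and ANCOVA does at about 0.69 to 0.70. A three-group repeated-measures F-test of the between-group effect, taking f = D/2 = 0.25 and a correlation of 0.5, needs 35.3 per group with three measurements and 32 with five. Each of these routes needs inputs that the article does not print; the paired test needs none.

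**A within-arm calculation suits the endpoint.** The endpoint is change from the participant's own baseline, and the analysis text speaks of the effectiveness of individual programmes. Nowhere does the article attach the 80% to product versus control. This is fair, and it supports reading 34 as a within-arm figure. But then the plan states neither a target difference nor a power for the comparisons it randomises for.

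**The missing inputs may be in the supplementary protocol.** They may. The point is not that an article omits detail. The inputs it does print reproduce a test that differs from the randomised comparison.

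**A reader might infer that the trial has only 69% power against control.** The documents do not support that as a plain fact. The figure requires D to be the between-arm difference, SD = 1 to be the SD of the analysed change, 220 rather than 240 participants, and no correction. Under the raw-SD reading, a moderately high baseline correlation would bring power to 80% or more, unadjusted.

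**Conclusion.** The concern holds in a conditional form. The printed inputs yield 34 as the size of a one-arm before-after test, and nothing printed turns it into a between-arm size. The 80% is therefore not shown to apply to the contrasts with control.

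If 0.5 is the between-arm difference in SDs of the analysed change, power against control is short of 80% after the assumed loss at either enrolment figure, and the promised correction widens the gap. Innovative versus standard exceeds 80% unadjusted but falls below it at alpha/3.

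Whether there is a real shortfall against control cannot be settled from the article, because it turns on the meaning of D and SD = 1 and on the baseline correlation. The documents support the conclusion that the power claim is unattributed; they do not prove that the trial is underpowered.

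**What to change.** Keep the enrolment and rewrite the sample-size paragraph so that it does the following:

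1. States which test and which contrast 34 and 80% refer to, with sidedness, number of measurements and any correlation used.
2. States whether SD = 1 is the SD of the change or of the raw value, and the kilograms it stands for.
3. Reconciles 220 with 240.
4. Prints, for each randomised contrast at the planned number of completers, the power and the detectable difference, both unadjusted and at the corrected alpha, with the correction named. If SD = 1 is the SD of change, the unadjusted detectable difference from control is 0.57 SD at 75:37 or 0.54 SD at 82:41.
5. Does not present 80% as the power against control unless a stated and justified correlation supports it.

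The cost is the rewording of one paragraph and no extra participants. The drawback is that the printed power against control may become less favourable.
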